### Monitoring

In each of the four regions, a Steering Committee member will have participated in the design of GET UP and will review the progress of the study and, if necessary, will agree changes to the protocol. A data monitoring committee is not needed here as it is a low-risk trial, not involving any pharmaceutical substances.

An interim analysis is performed on the primary endpoint when 50% of patients have been randomised and have completed the SF-12 and the PEDT 1 month after the inclusions. The interim analysis will be performed by the statistician, blinded to the treatment allocation. The statistician will report to the data manager. The data manager will have unblinded access to all data and will discuss the results of the interim analysis with the Steering Committee in a joint meeting.

The Steering Committee will decide on the continuation of the trial and will report to the Central Ethics Committee. The Steering Committee will also declare the end of the study. It may decide to stop the study if the inclusion rate is too weak or for administrative reasons.

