three attitude-related strategies for revealing the problem:Being particularly receptive to the patient throughout the consultation: especially at the end when the physician was about to open the door, in order to create a gap that the patient could use to express his problem. The physician consciously creates an attentive environment, using non-verbal behaviour which will encourage the patient to speak freelyUsing humour: lightening the atmosphere by using gentle humour without being vulgar or insensitiveTaking a matter-of-fact approach to play down any embarrassment in the patient’s view of sexuality: emphasising the natural and mechanical function of sexuality allows the GP to play down the emotional aspect of the subjectThree investigative strategies with interviews deliberately directed towards sexual dysfunction:Systematic questioning during consultations dedicated to preventionSymptoms that the patient could be experiencing: the GP suggests a list of signs and symptoms connected to the current clinical situation, for instance: ‘you’re presenting symptoms of depression, and depression may bring on physical, psychological, and even sexual tiredness’. The patient chooses one of these to talk about his PEFacilitating the patient’s verbal expression, enquiring about the patient’s psycho-social and medical history and his daily environment enables the subject of PE to be raised

The training session will be provided by the Steering Committee member in each of the four regions. Their expertise is as follows: three have had specialised training in sexology and three have had specialised training in education. They will receive audio-visual training in the presentation of the slides to ensure the replication of the intervention. GPs will be trained, with practice situations, using role-play performed with the committee member and the other GPs. Available treatments, based on the ‘guidelines for the diagnosis and treatment of premature ejaculation’ [8] will be presented during the session. The session will end with the presentation of the outcome questionnaires.

The intervention session will follow this agenda:30 min will be devoted to brainstorming1 h to the presentation of theoretical elements, and2 h will be devoted to role-play practice situations

The intervention will occur at the GP’s surgery or during a professional meeting, depending on the choice of the GP.

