#### Statistical methods

Analyses will be performed using Stata software, version 13 (StataCorp, College Station, TX, USA). All data will be analysed on intention to treat. The tests will be two-sided, with a type I error set at *α* = 0.05. Baseline characteristics (GPs and their patients) will be presented for each randomisation group as the mean ± standard deviation (SD) or the median (interquartile range) according to statistical distribution for continuous data and according to the number of patients and associated percentages for categorical parameters.

The comparisons between the randomised groups will be carried out using the Student *t* test or the Mann-Whitney test where appropriate, (1) normality verified by the Shapiro-Wilk test and (2) homoscedasticity by the Fisher-Snedecor test for quantitative parameters and using chi-squared or Fisher’s exact tests for categorical variables.

Outcomes will pertain to the cluster level using usual statistical tests and with more specific approaches at the individual level. Hierarchical regression models (generalised linear mixed model due to binary endpoint) will be performed as primary analysis: (1) to estimate the effect of intervention on the incidence of new cases of patients suffering from acquired and lifelong PE, natural variable PE and premature-like ejaculatory dysfunction and (2) to take into account the variability between and within, the GP cluster groups. Intra-class correlation coefficients will be presented by arm with a 95% CI. Then, GP characteristics (gender, age, geographical area) or patient characteristics (age, socioeconomic status) should be considered as covariate (fixed effects in mixed models) in adjusted multivariable analyses. The adjusted and unadjusted results will be presented: absolute numbers of patients who have raised the topic of PE with their related GP, relative risks and 95% CIs.

For secondary endpoints, comparisons at the individual level between randomised groups will be performed using an analysis of covariance for correlated data with the baseline score as a covariate, as suggested by Klar and Darlington [31] for the SF-12 quality of life scores. Results will be expressed as effect-sizes and 95% CIs. The PEDT will be analysed as a quantitative score using statistical methods described for the SF-12 quality of life and as a binary outcome (< ≥ 11) with the use of a generalised linear mixed model.

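### The interim analysis of the primary endpoint can pass mid-trial results to the committee that runs both arms' sessions, and the plan does not say whether it may support an efficacy claim

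*Protocol article*

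**What the plan says.** The Monitoring section sets out four steps.

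- **Timing and endpoint.** "An interim analysis is performed on the primary endpoint when 50% of patients have been randomised and have completed the SF-12 and the PEDT". These are the questionnaires due a month after inclusion.
- **Who analyses.** "The interim analysis will be performed by the statistician, blinded to the treatment allocation". The statistician reports to the data manager.
- **Who hears the results.** "The data manager will have unblinded access to all data and will discuss the results of the interim analysis with the Steering Committee". Both sides attend the same meeting.
- **Who decides.** "The Steering Committee will decide on the continuation of the trial". Its decision is then reported to the ethics committee.

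The same section says that a data monitoring committee is not needed because the trial is low-risk. It lets the Steering Committee agree protocol changes. The stopping reasons it names are too weak an inclusion rate and administrative reasons.

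On the Committee's other role, the Intervention section says: "The training session will be provided by the Steering Committee member in each of the four regions". The Usual care section gives the same members the control session. On the error rate, Statistical methods says: "The tests will be two-sided, with a type I error set at *α* = 0.05". It makes no link to the interim analysis.

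**The concern.** There are two separate issues.

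**Disclosure.** The outcome is whether PE is raised in a consultation, which depends on what the GP does. Intervention GPs are unblinded, and they invite patients after hearing the reason for the visit. The Blinding section wants control GPs not to know that they are controls, and wants the researchers to analyse without allocation information. A meeting in which an unblinded data manager discusses primary-endpoint results with the people who trained one arm and briefed the other works against both aims. If the effect became known, it could colour later contact with GPs, reminders or protocol changes. No analysis method can remove that afterwards.

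**Purpose of the look.** A continuation decision follows a primary-endpoint analysis, but the plan does not say whether a favourable result may end the trial or support a claim. If it may, an undivided 0.05 at the end does not hold the 5% error rate. If it may not, the look serves none of the stated stopping reasons.

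**Working it through.** **1. The plan's own figure.** Inputs from Sample size estimation: 5% v 20%, two-sided alpha 0.05, power 90%. With pooled variance and mean rate 0.125:

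n = [1.960·√(2·0.125·0.875) + 1.282·√(0.05·0.95 + 0.20·0.80)]² / 0.15² = (0.917 + 0.584)² / 0.0225 = 100.06, rounded up to 101.

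The plan's 101 reproduces (as a per-arm number) with the full 0.05. No alpha was set aside for an interim look.

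**2. Information fraction at the interim.** Design effect = 1 + (m − 1)·ICC, as in the plan. Effective patients per arm = 150 / design effect at the interim, and 300 / design effect at the end with m = 15. The fraction t is their ratio. The plan gives ICC 0.05 to 0.20. It does not give the accrual pattern, so I assume two extremes: half the GPs with complete clusters of 15, or all 40 GPs with 7.5 patients each.

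**3. Overall error if 0.05 were used at both looks.** With c = 1.96 and correlation √t between the two statistics:

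overall error = 1 − ∫ from −c to c of φ(x)·[Φ((c − √t·x)/√(1 − t)) − Φ((−c − √t·x)/√(1 − t))] dx

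| Accrual | ICC | Design effect | Effective per arm | t | Overall error | Interim power, 5% v 20% |
|---|---|---|---|---|---|---|
| Complete clusters | 0.05 | 1.70 | 88.2 | 0.50 | 8.3% | 86% |
| Complete clusters | 0.20 | 3.80 | 39.5 | 0.50 | 8.3% | 52% |
| 7.5 per GP | 0.05 | 1.325 | 113.2 | 0.64 | 7.8% | 93% |
| 7.5 per GP | 0.20 | 2.30 | 65.2 | 0.83 | 6.9% | 74% |

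If no efficacy claim can be made at the interim, only the final test counts and the error stays at 5%.

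**4. Boundaries, if a comparative look were kept.**

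- Haybittle-Peto: p < 0.001 at the interim and 0.05 at the end gives 0.0502 overall at t = 0.5, and less at larger t.
- O'Brien-Fleming-type spending on each 0.025 side: interim level = 4·[1 − Φ(2.241/√t)]. At t = 0.5 this is 0.003, with 0.049 at the end. At t = 0.64 the pair is 0.010 / 0.047, and at t = 0.83 it is 0.027 / 0.042. The levels must therefore be set at the realised information fraction.

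**5. Disclosure.** No arithmetic applies. Under Monitoring, results go from a blinded statistician to an unblinded data manager and then to the Committee. Under Intervention and Usual care, the Committee's regional members deliver both sessions. No sentence restricts what is shared, and no independent body stands between.

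**The case against.** **No efficacy stop is stated.** This stands. The named stopping reasons are recruitment and administration, and the general 0.05 in Statistical methods is not described as the level spent after an interim look. A reader might infer that the trial's error rate is 8.3%. The documents do not support that: the figure needs an efficacy claim at 0.05 at the interim and an information fraction of 0.5. It does not follow that the text excludes such a claim. It says that the Committee may stop for those reasons, not only for those, and neither reason needs a primary-endpoint analysis.

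**A boundary may be in an analysis plan or full protocol that is not shown.** This also stands, and its absence from the article is not the point here. A boundary elsewhere would not change the disclosure route that the article does state.

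**The statistician is blinded, and results by arm are not mentioned.** This is correct. A reader might infer that the Committee will be shown the effect by arm. The text does not say so; the data manager's access makes it possible and nothing prevents it. It is a risk, not a stated procedure.

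**The sessions normally come before a GP recruits.** This is fair. Mid-trial influence would run mainly through the monthly calls, the twice-monthly e-mails and any protocol changes, which narrows the route but does not close it.

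**The look is too weak to inform anyone.** A reader might add this on the strength of the 52% interim power. It does not hold: across the plan's ICC range and the two accrual patterns, interim power runs from about 52% to 93%.

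**Conclusion.** The concern holds as a risk of operational bias arising from a route that the plan itself lays down: primary-endpoint results at 50%, an unblinded data manager, and a deciding committee whose members deliver both arms' sessions, with no limit on what is shared. Its size cannot be calculated from the documents. It rests on the stated roles, not on any assumption about alpha.

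The error-rate part is conditional. It is about 6.9% to 8.3% in place of 5% if success may be declared at 0.05 at the interim, given ICC 0.05 to 0.20 and accrual between complete and half-filled clusters. It is exactly nil if no such claim is possible. The text leaves this open. The change is cheap and worth making, but it must come before the look, because disclosure cannot be undone.

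**What to change.** **Preferred.** Replace the interim analysis by a check pooled over arms of recruitment, overall event rate, ICC and missing data. State that no between-arm comparison is made, that the check supports no efficacy claim, and that the final test stays at two-sided 0.05. This serves the stopping reasons already named. An ICC estimated without regard to arm absorbs any arm effect and so tends to read high; say so in the text.

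**If a comparative look is kept.** Name the boundary: for example Haybittle-Peto at p < 0.001 with the final test at 0.05, or O'Brien-Fleming-type spending (0.003 / 0.049 at half the information, recomputed at the realised fraction). The statistician can apply a two-sided boundary to coded arms and remain blinded. The Steering Committee receives only 'continue' or 'boundary crossed', never results by arm.

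**Cost.** One paragraph. The Committee loses sight of mid-trial results by arm. The alpha cost is nil without the look and negligible with Haybittle-Peto. With O'Brien-Fleming-type spending it is small: at a final level of 0.048 the individual-randomisation figure rises from 101 to 102 per arm. At 0.042 (t = 0.83) it rises to 105, since (2.032·0.4677 + 0.584)² / 0.0225 = 104.6.

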#### Harm

In our study, no drugs will be used. No adverse outcome is defined.

#### Auditing

A clinical research associate commissioned by the promoter will ensure the successful completion of the study, the collection of data generated in writing and documentation, and will record and report in accordance with the standard operating procedures of the DRCI Brest and in accordance with good clinical practice and the laws and regulations in force.

The investigator and his team members agree to make the data available during the quality control visits at regular intervals by the clinical research associate. During these visits, the following items will be reviewed:

##### Informed consent

Compliance with the study protocol and procedures defined thereinQuality of data collected in the case report: accuracy, missing data, data consistency with the documents ‘source’ (medical records, appointment books, etc,)

Moreover, investigators undertake to accept quality assurance audits by the promoter as well as inspections by the competent authorities. All data, all documents and reports may be subject to audits and regulatory inspections.

## Discussion

This intervention study will be the first concerned with PE in the area of primary health care. Six different strategies for tackling the subject were brought to light after a qualitative phase with GPs was compared with usual care procedures in primary health care. A French version of the Premature Ejaculation Diagnostic Tool will be used to detect patients from the IG and the CG who suffer from PE.

One major limitation is the unblinded GPs in the IG. As the intervention is based on training in strategies to tackle PE, it was impossible to leave them blind to the main aim of the study. The evaluation of the diagnosis of PE will be made by the GP. This limitation is counterbalanced by the fact that the PEDT sent after 1 month will also contribute to making the positive or negative diagnosis of PE.

We selected our participants via an e-mail, mentioning a study on ‘sexual dysfunction’ at the first step of the study. We wanted to inform them about the topic raised during the intervention. The GPs in the CG knew that the study was investigating sexual dysfunction: this could lead to increased awareness of sexual dysfunction, including PE, and thereby lead to an increase in the rate of consultations where PE was raised. We did not mention ‘sexual dysfunction’ on any other occasion to the CG.

The definition of PE references a pathology concerned with ‘vaginal penetration’. However, we want to enlarge the study to include men with a different sexual orientation. We did not include any questions about heterosexual or homosexual orientation in our questionnaires.

The investigation of an intervention involving six communication strategies and the development of a sexual health communication tool for use in primary care would meet the needs of both practitioners and patients [32]. Implementing the strategies in a real practice context is the main added value of this trial. The ISSM guideline states that GPs have an important role to play in the diagnosis and treatment of PE [9]. This trial provides a pragmatic way to help the GPs to do this. The chosen format of an intervention lasting 4 h, and the rapid questionnaire to complete, were adapted to the time requested by the study and available for the GPs. A cluster design was chosen for pragmatic reasons and to avoid contamination bias. Doing pragmatic research in real practice is quite unusual for French GPs. The strategies are not exclusive to PE and may be useful for initiating discussion of other crucial issues related to sensitive topics. This concrete step of ‘how to do that in practice and how to be sure that it is efficient’ is often lacking in primary care. We wanted to connect research and practice in order to make the conclusions helpful for patients.

### Trial status

The study has not completed patient recruitment at the time of submission.

The Standard Protocol Items: Recommendations for Interventional Trials (SPIRIT) Checklist is included as Additional file 1. The Consolidated Standards of Reporting Trials (CONSORT) Checklist is incuded as Additional file 2.The Template for Intervention Description and Replication (TIDieR) Checklist is incuded as Additional file 3. The abstract of the linguistic and cultural validation procedure to obtain a French version of the Premature Ejaculation Diagnostic Tool (PEDT) is incuded as Additional file 4.

## Abbreviations

CG: Control group
CPP: Comité de Protection des Personnes
GP: General practitioner
IG: Intervention group
ISSM: International Society of Sexual Medicine
PE: Premature ejaculation
PEDT: Premature Ejaculation Diagnostic Tool
